### 9.6 UNANTICIPATED ADVERSE DEVICE EFFECTS

An UADE is defined as any serious adverse effect on health or safety or any life-threatening problem or death caused by, or associated with, the device if that effect, problem or death was not previously identified in nature, severity or degree of incidence in the investigational plan; or any other unanticipated serious problem associated with the device that relates to the rights, safety or welfare of subjects.

#### 9.7 REPORTING OF ADVERSE EVENTS

AEs observed during the course of this study, regardless of severity or relationship to the study participation will be recorded on the appropriate Adverse Event Form and reported to the Sponsor.

For sites and reporting to FDA, the procedures for handling and reporting/notification of SAEs shall be carried out in accordance with the applicable sections of 21 CFR Part 812 and local IRB requirements.

##### 9.7.1 Investigator Safety Reporting Requirements

SAEs will be recorded in the Adverse Event Form and the event is to be reported to the Sponsor within 24 hours of knowledge of the event. Information not available at the time of the initial report must be documented in the Adverse Event Form within 24 hours of receipt of the new information. Substantiating data such as relevant hospital or medical records and diagnostic test reports should also be submitted by scan/email to the Sponsor.

An Investigator shall submit to the Sponsor and to the reviewing IRB a report of any UADE occurring during an investigation as soon as possible, but in no event later than 10 working days after the investigator first learns of the effect. The Investigator must adhere to all reporting requirements for his IRB and national authorities.

##### 9.7.2 Sponsor Safety Reporting Requirements

SAEs and UADEs will be reported to the FDA, in accordance with 21 CFR Part 812.

In the event of a UADE, Sponsor will immediately conduct an evaluation of a UADE, and report the results of such evaluation to FDA and to all reviewing IRB's and participating investigators within see above comment. The Sponsor first receives notice of the effect. Thereafter, the Sponsor shall submit such additional reports concerning the effect as FDA requests.

#### 9.8 REPORTING PERIOD

In this study, all adverse events are collected starting at the time informed consent has been signed. AEs are collected until the last study visit and exit from the study.

#### 9.9 SAFETY MONITORING AND REPORTING

All observed or volunteered adverse events or suspected causal relationship to the investigational product will be reported as described above. For all adverse events, the PI will pursue and obtain information adequate to determine the outcome of the adverse event and to assess whether it meets the criteria for classification as a serious adverse event requiring immediate notification to the Study Sponsor or its designated representative. For all adverse events, sufficient information should be obtained by the investigator to determine the causality of the adverse event. The PI is required to assess causality. Follow-up by the investigator may be required until the event or its *sequelae* resolve or stabilize at a level acceptable to the investigator, and the Study Sponsor concurs with that assessment.

This study will involve a Data Safety Monitoring Board (DSMB) because this study will include participants who are at risk of attempting suicide. Oversight of the study is provided by the site PIs who will be actively involved in the conduct of the study. The PIs will lead ongoing and systematic reviews of data integrity, protocol adherence, and participant safety. Considering

the high risk and ethical concerns when doing research on suicide, the site PIs will ensure these two monitoring components are followed: 1) the clinical/safety monitoring of individual participants; 2) review of study data to assure data accuracy and consistency. DSMB members will include individuals who have extensive experience in clinical trials and suicide prevention. Site PIs will monitor data to determine whether study participation is leading to increased risk of harm to subjects by comparing rates and types of harm events across treatment arms. The DSMB will guide our team in assessing the risk of potential liability and matters of safety monitoring. During interim looks at the data for safety, the sponsor will continue to be blinded to condition, as will the assessors. The data will be tabulated by a CRO and forwarded to a DSMB for adjudication. There will be standard operating procedures for the DSMB meetings. Safety events/SAEs are clearly defined elsewhere in the protocol, with stopping rules (see section 11.5 STOPPING RULES). Safety events and SAEs will be reported to the DSMB for review by the DSMB in a timely manner (i.e. within 5 days). The study personnel and sponsor will remain blinded until all enrolled participants have completed the 104 week follow-up. If the DSMB requires the study be stopped (either for SAEs or positive outcomes/benefit), the study will be unblinded and a decision will be communicated to the Sponsor. The sponsor will notify the FDA.

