| Medication Use                                                                                                               |  |                              | X         |           |                    | X          | X          | X          | X                | X          | X          | X          |

\*Visit refers to the follow up contact via telephone between Principal Investigator (PI) or designee and the study participant  
a: Screening will be conducted while participants are in an inpatient psychiatric facility  
b: Form to collect demographic, medical history and contact information  
c: App is downloaded before the end of the study visit  
d: Assessments/scales/interviews administered by research team on a phone call with patient  
e: Logins since the last assessment period will be recorded in the source documents & eCRF

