## 4. STUDY DESIGN

### 4.1 OVERALL DESIGN

This double-blind RCT will evaluate the effectiveness of **Aviva + TAU versus a Sham + TAU** among 391 participants, adult inpatients, who had recent suicidal ideation with intent or suicide attempts. Study participation starts when consent is signed and patients are ready for discharge from an inpatient or emergency unit. Participants and assessors will be blinded to treatment assignment. The study is planned to take a total of 104 weeks from first patient randomized (52 weeks for enrollment, up to 104 weeks for patient follow up). An additional 4 months is planned for study close out. The primary endpoint will be analyzed in a group sequential design with looks at 60%, 75%, 90% and 100% of the expected number of suicide attempts. Overall Type I error (alpha) will be less than 0.025 one-sided.

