#### **9.9.1 DSMB Charter, Interim Analysis, and Statistician Blinding**

An independent statistician will provide the DSMB with the tables and analyses for the DSMB meetings. The independent statistician will participate in the DSMB meetings as a non-voting member and will be a different person from the statistician who is a member of the DSMB. Appropriate firewalls will be in place so that all persons involved with the operations of the study remain blinded to study results (the sponsor and researcher assessors will be blinded), except if the DSMB recommends stopping the study. In that case, members of the executive committee of Oui, the study investigators may be unblinded. This information will be included in the finalized DSMB charter when it becomes available. The finalized DSMB charter will be available once the DSMB is constituted and the Statistical Analysis Plan (SAP) has been finalized. Avania, a clinical research organization, will play the role of the independent statistician. The charter and DSMB will be convened in advance of opening study for enrollment.

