## **10. CLINICIAN TRAINING AND SUPERVISION**

### **Overview**

Oui Therapeutics or Consultants for the Study Sponsor, who are clinical psychologists with extensive experience administering and supervising assessment interviews within the context of clinical trials along with other experienced clinical trial professionals, will train the site PI's on the full battery of assessments for this research and existing protocols. The PI's will train the research therapists on the study protocol. The training will primarily focus on how to build rapport with the participant while they are in the hospital and establish a collaborative agreement to monitor suicidal ideation. The training will also include procedures for recruitment, enrollment, assessment and app installation, as well as safety protocols. The site staff will be trained to answer participant questions. If study participants self-identify changes in their condition, i.e. increased suicidal intent or behavior, the app will guide them to contact the PI for follow-up assessments. As part of their supervisory role, PIs are responsible for recruitment, enrollment, assessment, app installation, tracking outcomes, safety protocols, and ongoing participant care following enrollment.

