### 11.5 STOPPING RULES

A Data Safety and Monitoring Board (DSMB) will have oversight over the three stopping rules proposed below. Though we have proposed stopping rules within this protocol, the DSMB will finalize the stopping rules for safety. Safety Monitoring will be guided by previous research and study data to determine whether there is an excess of suicide attempts or death. Prior research has shown that, following a suicide attempt, up to half of the patients in treatment make another suicide attempt. If a suicide attempt occurs within the first year of treatment, on average a patient will attempt suicide 2.5 times. Monitoring of suicide attempts will occur by tracking hospitalization records, reviewing medical records, and carrying out interviews at all time points. Other specific strategies for tracking include (1) utilization of research staff ("study managers") to obtain detailed contact information regarding participants' family, friends, clergy, probation officers, and mental health workers and (2) research staff will use medical records and coordinate with the participants' healthcare providers, whenever possible, to track participants over time and to assist with scheduling follow-up assessments. If participants cannot be contacted, family, friends, clergy, probation officers, and mental health workers will be contacted by research staff with permission from the participants. The DSMB may recommend stopping the study if there is:

1. Early demonstration of effectiveness (assessed through the group sequential design) for suicide attempts. Effectiveness boundaries have been fully specified in Appendix C.
2. Early demonstration of lack of effectiveness for Aviva (assessed by specifying the group sequential design with binding futility). Futility boundaries have been fully specified in Appendix C.
3. Determination of unexpected, significant or unacceptable risk to participants by the monitoring committee. Based on historical prevalence of suicide attempts in this target population, we anticipate that up to half of enrolled patients could attempt suicide during a 104 week follow-up assessment period. DSMB will review all suicide attempts for causality to the investigational device, and if there are more SAs in the treatment arm than control arm, the study enrollment will be paused until DSMB can review under this stopping rule.

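### Sections 9.9 and 11.5 would expose arm-level harm results, or their direction, to site PIs, sites and sponsor, against the blinding and firewall promised in 9.9 and 9.9.1

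*Protocol*

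**What the plan says.** **Who compares the arms.** Protocol 9.9 assigns site PIs to monitor the data for "increased risk of harm to subjects by comparing rates and types of harm events across treatment arms".

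**Who stays blinded.** Later in 9.9: "The study personnel and sponsor will remain blinded until all enrolled participants have completed the 104 week follow-up". Section 9.9.1 requires firewalls so that "all persons involved with the operations of the study remain blinded to study results"; its parenthesis names the sponsor and the assessors. It allows investigators to be unblinded only if the DSMB recommends stopping. Section 4.1 is narrower: "Participants and assessors will be blinded to treatment assignment".

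**What the PIs do.** Section 10: "PIs are responsible for recruitment, enrollment, assessment, app installation, tracking outcomes, safety protocols, and ongoing participant care following enrollment". A footnote to Table 1 (1.4) reads: "Visit refers to the follow up contact via telephone between Principal Investigator (PI) or designee and the study participant".

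**The pause.** Section 11.5 item 3: "if there are more SAs in the treatment arm than control arm, the study enrollment will be paused until DSMB can review". It gives no minimum count, margin or checking interval, and does not say how the reason for a pause is kept from blinded staff. The opening of 11.5 describes the rules as proposed and leaves the DSMB to finalize those for safety.

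**The concern.** Comparing harm rates across arms requires data split by arm. Section 3.2.3 lists suicide attempts among the primary anticipated adverse events, so the harm being compared includes the primary-endpoint event. A PI who carries out the 9.9 instruction knows how the primary endpoint is running by arm, and is also responsible for assessment and outcome tracking at the site.

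The pause leaks by another route. Sites and sponsor cannot miss a stop in enrollment. The only ground that 11.5 names for pausing enrollment is an excess in the Aviva arm, so anyone who holds the protocol can infer that Aviva has the higher count even if no reason is announced.

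The stake is trial conduct. Attempts are identified by SASII interview supplemented by medical record review. People who supervise that work, or decide how the trial continues, should not know the by-arm results in a study that 2.1.2 calls pivotal.

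**Working it through.** **1. The passages side by side**

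| Instruction | Who | What follows |
|---|---|---|
| 9.9, harm comparison | Site PIs | Must see data by arm |
| 9.9, blinding | Study personnel and sponsor | Must not, until week 104 is complete for all |
| 9.9.1, firewall | All persons in operations | Must not see results |
| 10, PI duties | Site PIs | Are operational persons |

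The first row cannot be carried out together with the other three, and nothing in the protocol reconciles them.

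**2. The plan's own event figure, to confirm the inputs**

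From Attachment C: sham hazard 0.0115 per month, HR 0.3826, drift 3.4387, 195 sham and 196 Aviva, uniform accrual over 12 months, 24 months in total.

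- Events = 4 × drift² / (ln HR)² = 4 × 3.4387² / (ln 0.3826)² = 51.2, which rounds up to the stated 52.
- Share with an event by month 24 = 1 − (e^(−12λ) − e^(−24λ)) / (12λ). This gives 36.3 sham + 14.9 Aviva = 51.2, rounded up by arm to the stated 37 + 15.

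The plan's figures reproduce.

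**3. First attempts expected during accrual**

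Share with an event by month 12 = 1 − (1 − e^(−12λ)) / (12λ). Sham: 12λ = 0.138, which gives 12.9 events among 195. The HR of 0.6 is an assumed intermediate value.

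| HR | Sham | Aviva | Total |
|---|---|---|---|
| 0.3826 (design) | 12.9 | 5.1 | 17.9 |
| 0.6 | 12.9 | 7.9 | 20.8 |
| 1 | 12.9 | 12.9 | 25.8 |

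All three totals lie below the first planned look, at 31.2 events.

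**4. Chance that Aviva is ahead at some point during accrual**

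The probability that the next first attempt falls in the Aviva arm is approximately q = 196·HR / (196·HR + 195), that is 0.278, 0.376 and 0.501. If counts are checked after every event, the rule fires when a walk stepping +1 with probability q and −1 otherwise first reaches +1. Over 18, 21 and 26 events the exact probabilities are 0.382, 0.584 and 0.847. As a hand check, the unlimited-horizon value at the design HR is q / (1 − q) = 0.278 / 0.722 = 0.385.

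The checking frequency matters, so the two sparser schedules were simulated with the same hazards and accrual (accurate to about one percentage point):

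| Checking schedule | HR 0.3826 | HR 0.6 | HR 1 |
|---|---|---|---|
| After every first attempt | 38% | 58% | 85% |
| Quarterly | about 23% | about 39% | about 71% |
| Months 6 and 12 | about 12% | about 26% | about 61% |

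All rows count first attempts only. The effect of counting repeat attempts was not computed, and 11.5 does not say whether they count.

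**The case against.** **The double blind is broken.** A reader might infer this, but the documents do not support it. Section 4.1 names participants and assessors as the blinded parties, and neither 9.9 nor 11.5 gives them anyone's allocation. Section 9.9 also says that sponsor and assessors stay blinded to condition during interim safety looks.

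**PIs do not collect the endpoint.** Section 12.3 gives data collection to research assessors, separate from PIs who may be treating the patient. Footnote d of Table 1 has the research team administer the SASII. Medical record review can establish an attempt without the interview. PI causality ratings play no part in the endpoint, which counts any actual attempt. This stands: the route to bias is indirect, through the PIs' responsibility for assessment and outcome tracking in section 10.

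**The pause rule is provisional.** The DSMB is to finalize the safety rules, and 9.9.1 leaves details to a charter that is not at hand and may govern how a pause is announced. This softens the second part of the point. It does not touch the site-PI instruction in 9.9, and the pause is the rule as written until it is changed.

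**A pause says little about the effect.** With continuous checking it fires in 85% of trials with no effect and 38% with the design effect, a ratio of about 2.2. At the design HR, 28 of the 38 points come from the very first event falling in the Aviva arm. Only enrollment time is exposed, and about 34 of the 52 events (52 − 18) come later. This is fair as to the strength of the evidence. The pause would still disclose which arm had more attempts at that time, which the firewall is there to prevent.

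**Conclusion.** The point holds as an internal contradiction, with a second leak of more limited reach. The site-PI comparison in 9.9 is incompatible with the blinding of study personnel in 9.9 and with the firewall in 9.9.1. The pause in 11.5 item 3 would tell sites and sponsor the direction of primary-endpoint events while enrollment is open.

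What is exposed is arm-level results, or their direction, to PIs, sites and sponsor. The individual allocation blind of participants and assessors is not shown to fail.

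The chance of a pause during accrual runs from about 12% (design HR, checks at months 6 and 12) to 85% (no effect, checks after every event). These figures assume the plan's sham hazard, exponential times, uniform 12-month accrual and first attempts only. The protocol fixes no checking frequency, so no single figure can be given. That the reason for a pause would be understood is an inference from the rule's wording; no section says that sites would be told.

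**What to change.** - **Section 9.9:** delete the site-PI comparison across arms. Limit PIs to individual cases and arm-pooled safety data, and give by-arm comparison to the DSMB through the independent statistician already provided in 9.9.1.
- **Sections 11.5 item 3 and 9.9.1:** reconcile them so that by-arm counts are reviewed inside the firewall and any action reaches sites and sponsor without revealing arm or direction. Withholding the reason is not enough while the protocol that sites hold names an Aviva excess as the only ground for pausing enrollment. The criterion itself stays with the DSMB, as 11.5 already provides; none is proposed here.
- **Section 11.5 or the DSMB charter:** state how often counts are reviewed and whether repeat attempts count, so that the DSMB can know how often its rule would fire by chance.

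The cost is wording only. The DSMB, the independent statistician and the CRO tabulation are already in the plan.

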#### **9.9.1 DSMB Charter, Interim Analysis, and Statistician Blinding**

An independent statistician will provide the DSMB with the tables and analyses for the DSMB meetings. The independent statistician will participate in the DSMB meetings as a non-voting member and will be a different person from the statistician who is a member of the DSMB. Appropriate firewalls will be in place so that all persons involved with the operations of the study remain blinded to study results (the sponsor and researcher assessors will be blinded), except if the DSMB recommends stopping the study. In that case, members of the executive committee of Oui, the study investigators may be unblinded. This information will be included in the finalized DSMB charter when it becomes available. The finalized DSMB charter will be available once the DSMB is constituted and the Statistical Analysis Plan (SAP) has been finalized. Avania, a clinical research organization, will play the role of the independent statistician. The charter and DSMB will be convened in advance of opening study for enrollment.

## **10. CLINICIAN TRAINING AND SUPERVISION**

### **Overview**

Oui Therapeutics or Consultants for the Study Sponsor, who are clinical psychologists with extensive experience administering and supervising assessment interviews within the context of clinical trials along with other experienced clinical trial professionals, will train the site PI's on the full battery of assessments for this research and existing protocols. The PI's will train the research therapists on the study protocol. The training will primarily focus on how to build rapport with the participant while they are in the hospital and establish a collaborative agreement to monitor suicidal ideation. The training will also include procedures for recruitment, enrollment, assessment and app installation, as well as safety protocols. The site staff will be trained to answer participant questions. If study participants self-identify changes in their condition, i.e. increased suicidal intent or behavior, the app will guide them to contact the PI for follow-up assessments. As part of their supervisory role, PIs are responsible for recruitment, enrollment, assessment, app installation, tracking outcomes, safety protocols, and ongoing participant care following enrollment.

### **Specific strategies for obtaining complete records**

To obtain complete records before randomization, a research staff member at each site will be trained to collect information regarding inclusion/exclusion criteria. There will be a standardized form for the research staff to complete to document the presence or absence of inclusion and exclusion criteria and the source of the information. The form will contain specific

steps and procedures for collecting data from participant's medical record (e.g., search for self-injury and suicide attempt ICD codes [<https://www.cdc.gov/nchs/data/nhsr/nhsr108.pdf>]), the participant and the provider supervising the patient's care. A waiver of consent and HIPAA will be requested so that the study team can review medical records of potential participants to determine whether they are likely to be eligible for the study and the consent form will explain the procedures that were used. A research staff member will conduct the medical record search prior to the baseline assessment, then provide the list of identified events to the interviewer prior to baseline assessments.

To obtain complete medical records after randomization, structured follow-up assessments and electronic medical record reviews will be conducted by study staff.

- Follow-up assessments: The follow up assessments will be clinician-administered interviews designed to assess incidence of suicidal behaviors, adverse events and other variables of interest during the target assessment period. To reduce likelihood of missed follow-up assessments specific strategies for tracking will be used such as (1) utilization of research staff ("study managers") to obtain detailed contact information regarding participants' family, friends, clergy, probation officers, and mental health workers and (2) utilization of research staff who will use medical records and the participants' healthcare providers, whenever possible, to track participants over time and to assist with scheduling follow-up assessments. If participants cannot be contacted, family, friends, clergy, probation officers, and mental health workers will be contacted by research staff, with permission from the participants.
- Electronic Medical Records: Review of electronic medical records will be conducted to identify suicide attempts that might have been missed during assessment interviews (e.g., participants who drop out early or miss follow-up assessments) as well as to quantify use of mental health and medical services by participants (e.g., frequency and type of appointments, frequency and duration of inpatient hospitalization, etc.). We will conduct a search within the medical records for self-injury and suicide attempt ICD codes (<https://www.cdc.gov/nchs/data/nhsr/nhsr108.pdf>).

